# A randomized, open phase IV exploratory clinical trial to evaluate the efficacy and safety of acupuncture on the outcome of induction of ovulation in women with poor ovarian response

**DOI:** 10.1097/MD.0000000000011813

**Published:** 2018-08-24

**Keywords:** acupuncture, anti-Müllerian hormone, antral follicle count, IVF-ET, oocytes, poor ovarian responder

## Abstract

**Introduction::**

Women with infertility who have a poor ovarian responder (POR), characterized by a low number of retrieved oocytes after ovulation induction, often have a significantly reduced pregnancy rate after in vitro fertilization-embryo transfer (IVF-ET), due to the few transferred embryos. Acupuncture is a form of Korean Traditional Medicine. It involves the insertion of a microscopic needle at a specific point in the body, known as an acupuncture point or an acupoint. In this study, our purpose is to investigate how acupuncture affects the retrieval of mature oocytes after ovulation induction in patients with POR.

**Methods and analysis::**

This study will be a randomized clinical trial comprising an IVF-ET trial and an IVF-ET trial after acupuncture. Seventy patients will by enrolled and randomly assigned to either of the 2 groups. The study subjects will be required to be diagnosed as having POR. Participants will be divided into 2 groups: IVF-ET single treatment group, and acupuncture and IVF-ET combined treatment group. The study subjects will be required to participate in a 15-week trial involving 16 acupuncture treatments over a period of approximately 2 months before ovulation induction for oocyte retrieval. The primary assessment of all participants will be comparing the number of oocytes.

**Result::**

This treatment will be a therapeutic model for POR.

**Discussion::**

Our results will provide patients with POR as well as complementary and alternative medicine professionals, such as Korean medicine doctors, about the potential role of acupuncture in the treatment of POR. This will improve the quality of life in women with infertility and provide an important treatment option for patients with POR. Further studies can be performed to determine the optimal treatment for POR.

## Introduction

1

As World Health Organization (WHO) defined, infertility is a disease of the reproductive system defined by the failure to achieve a clinical pregnancy after 12 months or more of regular unprotected sexual intercourse.^[1]^ Also, if a patient does not become pregnant despite having a normal marriage for 1 year, the condition is defined as “infertility.” Infertility is reported to be present in approximately 10% to 20% of the population in the reproductive age group.^[2]^ In recent years, various factors, such as increased marriage age, labor intensity, and pollution, have been pointed out as causes for the high infertility rate; these affect approximately 40% of infertile couples.^[3]^ In approximately 15% of patients, the cause of infertility is disordered ovulation, while in 30% to 40%, it is obstruction of the fallopian tubes and/or issues in the abdominal cavity. There is an increasing demand for assisted reproduction techniques, namely in vitro fertilization and embryo transfer (IVF-ET) and artificial insemination, to address this problem.^[4]^ Specially, infertility patients with a poor ovarian responder (POR), which is characterized by a low number of retrieved oocytes after ovulation induction,^[5]^ have a significantly reduced pregnancy rate with IVF-ET due to the low number of transferred embryos.^[6]^ In this case, the most important goal of assisted reproduction technology is increasing the quality and quantity of oocytes.

Although the number of patients with POR is increasing due to various reasons, there is no standard treatment yet. Currently, many patients are using complementary and alternative medical (CAM) treatment therapies, such as acupuncture, moxibustion, and herbal formulas, to increase the success rate of IVF-ET. Acupuncture is a commonly used adjuvant therapy during these CAM therapies.^[7]^

Acupuncture involves the insertion of a microscopic needle at a specific point in the body, known as an acupuncture point or acupoints, as a form of Korean Traditional Medicine (KTM).^[8]^ Acupuncture has a superior safety profile when conducted by a Korean Medicine Doctor (KMD). Ninety percent of patients experience no side effects, and no large-scale events have occurred.^[9]^ In KTM, traditional therapy, including acupuncture and herbal medicine, has been widely used to treat infertility for many years, and many reports on these treatments exist. In 1999, Stener-Victorin et al revealed that acupuncture could increase the IVF clinical pregnancy rate.^[10]^ Since then, randomized clinical trials (RCTs) of acupuncture for treating various causes of infertility, such as POR,^[11]^ thin endometrium,^[12]^ and polycystic ovarian syndrome,^[13]^ have been ongoing. In this study, our purpose is to investigate how acupuncture could affect the retrieval of mature oocytes after ovulation induction in patients with POR.

## Patients and methods

2

### Research evidence and hypothesis

2.1

Clinical studies on the effects of acupuncture on the number of retrieved mature oocytes after ovulation induction and pregnancy success rate in patients with POR, especially in China, are underway, and a number of papers, including RCTs, have been published.^[14–16]^ Based on several previous studies, it was hypothesized that acupuncture treatment could increase the number of mature oocytes. To prove this, the current study was designed to investigate the effect of acupuncture treatment on mature oocytes after ovulation induction in patients with POR.

### Study design

2.2

This study will include only an IVF-ET trial and an IVF-ET trial after acupuncture treatment in the form of RCTs. Seventy patients will by enrolled and randomly assigned into either of the 2 groups of the trial. The trial will be conducted at the infertility center in Pusan National University (PNU, Busan, Republic of Korea, Trial protocol version: KI-17-D-001 Version 2.0, August 8, 2017). The study subjects will be required to be diagnosed as having POR. Participants will be divided into 2 groups: IVF-ET single treatment group, and acupuncture and IVF-ET combined treatment group. The entire flow chart of the study is shown in Fig. 1. The study subjects will be required to participate in a 15-week trial involving 16 acupuncture treatments during a period of approximately 2 months before ovulation induction for oocyte retrieval.

**Figure 1 F1:**
[figure not shown]
Trial overview.

### Study population

2.3

This study will be conducted in primary care at an infertility center in PNU. Eligible participants will include adult women who are diagnosed with POR and who require induction of ovulation in a procedure-based IVF-ET. Potential participants will be provided with sufficient information about the study, and only those who agree to the study protocol and sign the consent form will be enrolled. The study will be implemented according to the Good Clinical Practice (GCP) terms and the revised version of the Declaration of Helsinki.

### Power calculation

2.4

This study is a randomized, open phase IV, exploratory clinical trial to assess the efficacy and safety of acupuncture in adult women diagnosed with POR after induction of ovulation. The primary efficacy endpoint will be the number of mature oocytes collected at approximately 10 weeks. The sample size in this study will be calculated by referring to the results of a transcutaneous electrical acupoint stimulation (TEAS) study performed by Zheng et al, because there is no related study, although the same acupuncture study results should be referred to. According to Zheng et al, the number of mature oocytes was counted as 2.38 ± 1.55 in the control group and 4.87 ± 3.47 in the TEAS treatment group. The results of the experimental group were assumed to be the effect of TEAS, and the standard deviation (Stdev) was assumed to be the Stdev of 3.47. Based on the results of this study, 31 subjects were included to secure 80% of power with 5% to the bilateral significance and 1:1 of the dispensing ratio. If the dropout rate is 10%, 35 subjects in each group will be recruited.

### Recruitment, randomization

2.5

This study is open phase; therefore, random assignment codes will be assigned using the block randomization method. This will be done using SAS (Version 9.3, SAS Institute, Cary, NC), by a statistician who is not directly related to this clinical study. The statistician will distribute the randomization code to the person in charge of the clinical trial institution before commencing the clinical trial.

Subjects who will be enrolled in the study and who will meet the inclusion/exclusion criteria will be assigned to each application group in a randomized sequential envelope according to the random assignment number. This randomization number will be used as the study participant identification code during the trial. The entire process of the study will be directed by the authorized clinical research organization (CRO), CROcent Corporation, Seoul, Korea.

### Early termination or dropout

2.6

The criteria for early termination or dropout are as follows: withdrawal of consent of research subject or research subject agent; cases in which it is difficult to continue due to an adverse event; case violation of selection criteria or exclusion criteria during the clinical trial; when a combination of drugs is required that affects the safety/efficacy assessment; cases in which the subject cannot be followed up; cases where the trial was judged to be difficult to continue; and cases where the patient falls naturally pregnant

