## Discussion

4

Acupuncture is widely accepted by Koreans, and it is increasingly requested by patients with infertility. To date, it is difficult to assess the effectiveness of acupuncture due to a lack of RCTs on acupuncture for patients with POR. In this clinical trial, the Arm 1 group has been designed as the intervention group to determine the effectiveness of acupuncture. Patients diagnosed with POR will undergo 8 acupoints treatments for 8 weeks. The patients in the Arm 2 group will be asked not to take any alternative treatments except for rest during the 8 weeks. If this part is not implemented, it will have to be abandoned to complete the research. We will evaluate the quality and number of mature oocytes after acupuncture treatment for patients with POR. We will also observe the clinical pregnancy rate after IVF-ET.

This study can potentially identify whether acupuncture is effective as a POR standard therapy under stringent quality control. Our results will enable patients with POR and CAM professionals, such as KMDs, to determine the potential role of acupuncture in the treatment of POR. This has the potential to improve the quality of life in women with infertility as well as provide an important treatment option for patients with POR. Further studies will be required to determine the optimal treatment for POR, including acupuncture.

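### Natural pregnancy, mid-trial eligibility breaches and interfering drugs end participation after randomisation, so the once-only oocyte count can be lost informatively, and natural conception is counted in no listed outcome

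*Protocol article*

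**What the plan says.** Section 2.6 (Early termination or dropout) gives one list for both arms. Beside withdrawal of consent and loss to follow-up it names violation of the selection or exclusion criteria during the trial, need for drugs that affect the assessments, and "cases where the patient falls naturally pregnant". Exclusion criterion 2 (section 2.8.2) covers pregnancy-related medicines and procedures, with hormones, herbal medicine and moxibustion as examples.

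The Discussion says that Arm 2 women will be asked to take no alternative treatment during the 8 weeks, and continues: "If this part is not implemented, it will have to be abandoned to complete the research". The Introduction describes the patient population thus: "Currently, many patients are using complementary and alternative medical (CAM) treatment therapies".

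Sections 2.10.1 and 2.12.1 set the primary endpoint as the number of mature oocytes at 10 weeks from baseline. Section 2.11.3 handles missing continuous values by last observation carried forward. A further sentence there, whose wording is unclear, seems to bar carrying pre-treatment values across the start of treatment.

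Pregnancy appears in none of the outcome sections (2.10, 2.12). The Discussion alone says: "We will also observe the clinical pregnancy rate after IVF-ET".

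**The concern.** Randomisation is on day 2 of the menstrual cycle at baseline, and ovulation is induced about 8 weeks later, at the start of the third cycle. Any removal in that window follows allocation and may depend on it or on prognosis.

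Two things are at stake. The first is comparability. If the women removed differ between arms in number or in kind, the women who reach retrieval are no longer the randomised groups, and the difference in mean oocyte count is biased. The setting makes this plausible: the trial is open, Arm 2 has no treatment for 2 months, and the widest restriction on other therapies is worded for Arm 2 alone.

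The second is how a good result is recorded. Conception during the pre-treatment phase is what an infertility patient wants, and the study treatment could contribute to it. The plan files it with dropouts. The one pregnancy measure mentioned, in the Discussion, is tied to IVF-ET and so omits natural conceptions.

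**Working it through.** **1. The plan's sample size.** Inputs from section 2.4: "2.38 ± 1.55 in the control group and 4.87 ± 3.47 in the TEAS treatment group", SD 3.47 used for both arms, and "31 subjects were included to secure 80% of power with 5% to the bilateral significance and 1:1 of the dispensing ratio".

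- Difference = 4.87 − 2.38 = 2.49.
- n per arm = 2 × (1.960 + 0.842)² × 3.47² / 2.49² = 30.5, rounded up to 31.
- With 10% dropout: 31 / 0.9 = 34.4, rounded up to 35.

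Both stated figures reproduce. The t-test solution is 31.5 per arm, with power 79.4% at 31. The allowance is 70 − 62 = 8 women. Inflating from 31 to 35 treats dropouts as contributing no count.

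**2. What happens to a removed woman's primary outcome.** The oocyte count exists only at retrieval, at about week 10. If she leaves before then, no on-study count precedes it. A count from an IVF cycle before the trial is not an on-study value and appears to be barred by section 2.11.3. Last observation carried forward therefore yields nothing. If a removal for eligibility or co-therapy also stops her retrieval being recorded, no analysis set defined later can restore it. A naturally pregnant woman differs: she has no retrieval under any rule.

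**3. Who is reached in each arm.**

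| Rule | Arm 1 | Arm 2 |
|---|---|---|
| Natural pregnancy (2.6) | yes | yes |
| Interfering drugs (2.6) | yes | yes |
| Hormones, herbal medicine, moxibustion (2.6 with 2.8.2) | yes | yes |
| Any alternative treatment (Discussion) | not stated | apparently |

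Only the last row is specific to one arm.

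**4. Possible number of events.** The documents give no rates, so these are assumptions.

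- Natural conception at 1% to 3% per cycle over two cycles: 70 × (1 − 0.99²) = 1.4 and 70 × (1 − 0.97²) = 4.1 women in both arms together.
- Other therapy in 10% to 20% of Arm 2: 35 × 0.10 = 3.5 and 35 × 0.20 = 7 women.

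**5. Power.** Difference 2.49, SD 3.47, two-sided 5%. The normal approximation is Φ(2.49 / [3.47 × √(1/n₁ + 1/n₂)] − 1.960). The t-test figure uses the noncentral t distribution.

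| Evaluable, Arm 1 v Arm 2 | Normal | t test |
|---|---|---|
| 35 v 35 (no loss) | 85.1% | 84.1% |
| 35 v 31 (about 10% of Arm 2 lost) | 82.9% | 81.7% |
| 35 v 28 (20% of Arm 2 lost) | 80.8% | 79.5% |
| 32 v 32 (about 10% lost in each) | 81.9% | 80.7% |
| 32 v 28 (about 10% and 20%) | 79.2% | 77.8% |
| 32 v 24 (about 10% and 30%) | 75.7% | 74.2% |

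If the Arm 2 loss is taken from 31, with the whole allowance already spent on other dropouts, t-test power is 77.2% (31 v 28) and 74.6% (31 v 25).

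**6. Bias.** Let p₁ and p₀ be the shares removed from Arms 1 and 2, and k₁ and k₀ the amounts by which removed women's oocyte counts would have exceeded those of retained women. The difference among completers is then 2.49 − p₁k₁ + p₀k₀. All p and k are assumed.

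- 10% and 10%, both 2 better: 2.49 − 0.20 + 0.20 = 2.49.
- 10% and 5%, both 2 better: 2.49 − 0.20 + 0.10 = 2.39.
- 5% and 15%, both 2 better: 2.49 − 0.10 + 0.30 = 2.69.
- 10% and 10%, 2 better in Arm 1 and 1 worse in Arm 2: 2.49 − 0.20 − 0.10 = 2.19.

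The bias can go either way, and it vanishes when share and type are equal.

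**The case against.** The strongest reply is that section 2.6 concerns termination and does not say that these women leave the analysis. Analysis sets are commonly left to the full protocol or the SAP, neither of which is shown, and inflating for dropout is routine planning that defines no analysis set. This stands as far as it goes: a reader might infer that the plan deletes these women from the analysis, and the text does not say so. It does not dispose of the point, because an oocyte count never collected cannot be supplied by any analysis set.

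A reader might also infer that women are removed unevenly, or from Arm 2 only. The documents do not support that as fact. The section 2.6 rules cover both arms and, with exclusion criterion 2, already reach users of hormones, herbal medicine and moxibustion in both. The Arm 2 sentence is a Discussion remark whose subject is unclear, and it is not in the section 2.6 list. That untreated women would be the likeliest to seek other therapy is plausible but undocumented.

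The size argument largely stands as well. The 10% allowance is meant for losses of this kind, and a removal of 10% to 20% in one arm only, of women differing by 1 oocyte, shifts the contrast by 0.1 to 0.2, which is 4% to 8% of 2.49. Finally, the trial is called exploratory and its stated aim is oocyte retrieval. Imputing a hypothetical count for a naturally pregnant woman is one choice of estimand among several, so no single method can be called required.

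**Conclusion.** The point holds as a risk built into the removal rules. Followed as written, they can lose primary outcomes after randomisation that the stated missing-data method cannot replace, and they leave a favourable, possibly treatment-related event outside every listed outcome. Whether the loss would be uneven, and which arm it would favour, cannot be determined: the documents give no rate of natural conception or co-therapy use and no oocyte difference between removed and retained women.

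The power effect is small. By t test, power stays at about 80% or above if losses are near 10% in each arm, and falls to about 74% to 78% only if the allowance is used up and Arm 2 loses more. The reason to act is comparability between arms. The exploratory label does not remove it, since the Discussion expects the trial to inform whether acupuncture works as a standard therapy for this population. These figures rest on the plan's own effect and SD and on the assumed rates shown above.

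**What to change.** - In section 2.6, separate three things: ending or modifying study treatment, ending follow-up, and inclusion in the analysis. State that the listed events may affect the first but not the other two, apart from withdrawal of consent to follow-up. When treatment should stop is for the investigators and is not at issue here.
- Collect the oocyte count for every randomised woman who reaches retrieval, and analyse her as allocated.
- Record co-therapy in both arms under the same rule. Use removal of users only in a per-protocol sensitivity analysis.
- List clinical pregnancy, natural or after IVF-ET, per randomised woman as an outcome in sections 2.10 and 2.12. Make clear that the rule scoring missing categorical values as failures does not turn a natural conception into a failure.
- Prespecify how naturally pregnant women enter the oocyte comparison, and add a sensitivity analysis. Multiple imputation with a sensitivity analysis that ranks them best is one workable option.
- Reconcile sections 2.6, 2.8.2 and 2.11.3 and the Discussion, including what is to be abandoned and for whom.

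The cost is mainly wording, plus recording co-therapy and retrievals for women who would otherwise have been removed. Retained co-therapy users may dilute the effect slightly. The change is worth making before retrievals go unrecorded, since they cannot be recovered afterwards.

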### Clinical trial procedure

2.7

#### Screening period

2.7.1

Screening numbers will be assigned to the study subjects who have provided written consent, and then eligibility will be assessed using inclusion/exclusion criteria. The participants will measure the factors: demographic, medical history, and previous drugs. The subjects will be selected from the group based on physical examination, vital signs, physical examination, endometrial examination, endocrine test, laboratory test, serum test, pregnancy test, chest radiographs, and inclusion/exclusion criteria will be assessed to gather information.

#### Baseline

2.7.2

(1)The baseline is the second day of menstruation. On the second day, information will be collected by performing history confirmation, previous drugs, vital signs, anti-Müllerian hormone (AMH) test, antral follicle count (AFC) using ovarian ultrasound, random assignment, and evaluation with the depression anxiety stress scales (DASS) 42.(2)One-time after-screening randomization is performed at a ratio of 1:1 eligible subjects on the second day of menstruation.Arm 1: IVF-ET after acupuncture.Arm 2: IVF-ET.

#### Treatment period

2.7.3

(1)Arm 1: IVF-ET after acupunctureThe KMD begins acupuncture treatment from the random allocation date of the subjects. The subject will be administered acupuncture treatment at 2-day (+1 day) intervals until the beginning of the third menstrual period (approximately 8 weeks) for a total of 16 acupuncture visits.(2)Arm 2: IVF-ETThe subjects are not scheduled to visit a separate clinical trial until approximately 8 weeks (28 day ± 1) from the date of randomization, when they present for oocyte collection.

#### Ovulation

2.7.4

Arm 1 and Arm 2 groups start 3 cycles of menstruation from the random allocation day, and at the beginning of the third cycle, they visit the institute conducting clinical trials to induce ovulation.

### Criteria

2.8

#### Inclusion criteria

2.8.1

The subjects should meet all the following criteria.

1.Sex: female2.Age: 20 to 45 years3.Women who have voluntarily signed a written consent to participate in the trial4.Women who have had infertility for more than 1 year or who have been diagnosed with infertility in a medical institution5.Women who have been diagnosed with POR (including at least 2 of the following criteria)a.Advanced maternal age (≥40 years) or any other risk factor for PORb.A previous POR (≤3 oocytes with a conventional stimulation protocol)c.An abnormal ovarian reserve test (AMH < 0.5–1.1 ng/mL or total AFC < 5–7 follicles)6.Women who have the ability and willingness to take the test during the clinical trial period

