#### Primary assessment

2.12.1

The primary endpoint will be the number of mature oocytes harvested at 10 weeks from baseline. The descriptive for each applied group will be presented and analyzed with the 2-sample *t* test or Wilcoxon rank-sum test depending on the satisfaction of normality.

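### Criterion 5 mixes women with a documented low oocyte yield and women with only a predicted one, while the primary test is unadjusted and the conclusion does not distinguish them

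*Protocol article*

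**What the plan says.** The protocol article uses POR in two ways.

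- **Background.** The Abstract describes POR as "characterized by a low number of retrieved oocytes after ovulation induction", and the Introduction says the same: "which is characterized by a low number of retrieved oocytes after ovulation induction". Both point to something already observed in a stimulated cycle.
- **Entry rule.** Section 2.8.1, item 5, admits "Women who have been diagnosed with POR (including at least 2 of the following criteria". The three items are 5a, age 40 or over or any other risk factor; 5b, "A previous POR (≤3 oocytes with a conventional stimulation protocol"; and 5c, "An abnormal ovarian reserve test (AMH < 0.5–1.1 ng/mL or total AFC < 5–7 follicles".

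On allocation, section 2.5 says that "random assignment codes will be assigned using the block randomization method" and names no stratification factor. On analysis, section 2.12.1 states that the number of mature oocytes at 10 weeks will be "analyzed with the 2-sample *t* test or Wilcoxon rank-sum test depending on the satisfaction of normality". No covariate or stratum enters that comparison. The Abstract's discussion and section 4 draw their conclusions for patients with POR as a whole.

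**The concern.** Only 5b requires the event by which the Abstract and Introduction characterise the condition. Any two of the three items suffice, so the trial can enrol women with a documented yield of 3 or fewer oocytes alongside women whose low response is predicted and who may never have had a stimulated cycle.

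Item 5b is also the only entry item that counts oocytes from a stimulated cycle, which is nearly the scale of the primary endpoint. If it predicts the next yield, an analysis that ignores it leaves explainable variation in the error term. A reader who takes POR in the Introduction's sense could also apply the result to women with a proven low yield only, although the trial population is wider.

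**Working it through.** **1. The entry rule, enumerated.** Three pairs of items are enough to qualify:

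| Pair | Observed low yield required? |
|---|---|
| 5a + 5b | yes |
| 5b + 5c | yes |
| 5a + 5c | no |

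No other criterion in sections 2.8.1 or 2.8.2 requires a previous stimulated cycle. Women who enter on 5a + 5c alone may be unstimulated, or may have been stimulated without meeting 5b.

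**2. The plan's own sample size (section 2.4).** Inputs: means 2.38 and 4.87, so a difference of 2.49; SD 3.47; two-sided 5%; 80% power; 1:1 allocation.

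n per group = 2 × (1.96 + 0.8416)² × 3.47² / 2.49² = 30.5, rounded up to 31. With 10% dropout, 31 / 0.9 = 34.4, rounded up to 35. Both stated figures reproduce.

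**3. Precision of the planned comparison.** With SD 3.47 and 35 per arm:

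- SE = 3.47 × √(2/35) = 0.83; variance = 0.688
- 95% half-width = 1.96 × 0.83 = 1.63 oocytes

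**4. The part due to entry route.** The documents give neither the share of women without 5b nor the gap in mean yield between the two kinds of women. Assume a share of 50% and a gap of 1 to 2 oocytes.

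- SE of the arm difference in share = √(2 × 0.5 × 0.5 / 35) = 0.1195
- Variance contributed: (0.1195 × 1)² = 0.014 to (0.1195 × 2)² = 0.057
- As a fraction of 0.688: 2.1% to 8.3%

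Removing that part would shorten the half-width from 1.63 to 1.63 × √(1 − 0.021) = 1.61 or 1.63 × √(1 − 0.083) = 1.56. At a share of 25% the fraction is 0.25 × 0.75 × gap² / 3.47², which is 1.6% to 6.2%.

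The fraction depends on the SD. If the two SDs quoted in section 2.4 (1.55 and 3.47) each applied to one arm, the variance would be (1.55² + 3.47²)/35 = 0.413 and the 50% case would give 3.5% to 13.8%.

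**5. Effect on power.** Take 3.47 as the SD within each kind of woman and the same treatment effect in both. For shares of 25% to 50% and gaps of 1 to 2 oocytes, the overall SD is √(3.47² + share × (1 − share) × gap²) = 3.50 to 3.61. Power at 31 per group is then 80.0% to 77.5%, against 80.7% without mixing. Mixing alone costs little power.

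**The case against.** **The background clause does not define eligibility.** The Abstract and Introduction only characterise POR; criterion 5 is the working definition and openly lists a previous poor response as one of three items. This stands. A reader might infer that the conclusion is wrong for women entering on 5a + 5c, but that follows only if an introductory clause overrides the inclusion criteria. What remains is a mismatch of wording that leaves the scope unclear.

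**Stratification may exist elsewhere.** Section 2.2 identifies a full protocol that is not shown, and an article may omit stratification factors. This also stands: the article does not establish that the allocation is unstratified. It does state the primary test, however, and that test is unadjusted.

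**Chance imbalance is not an additional error.** With a 50% share, the 95% range for the imbalance is ±1.96 × 0.1195 = ±23 percentage points. Multiplied by 1 to 2 oocytes this is ±0.23 to ±0.47, and a reader might set that against 2.49 and call it a distortion of 9% to 19%. That would be a misreading, because this variation is already inside the ±1.63 of the unadjusted comparison.

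**Some premises lie outside the documents.** No section shows how strongly previous yield predicts the next one, or that women on 5a + 5c may respond normally; they must carry two POR markers. Larger losses (power of about 70% or 56% at shares of 25% or 50%) arise only if acupuncture works half as well in women without 5b, and nothing in the article supports that.

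**Imbalance would be partly visible.** Medical history, AMH and AFC are collected (sections 2.7.1 and 2.7.2), and section 2.11.4 compares population and clinical history data by group. That helps interpretation but does not recover precision.

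**Conclusion.** The point holds as one of precision and scope. Criterion 5 admits women with proven and with merely predicted POR, the stated primary test makes no use of the entry item closest to the endpoint, and the conclusions do not say which women they cover.

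The treatment comparison is not biased, and the unadjusted test remains valid. The gain from adjustment is modest: about 2% to 8% of the variance of the difference, with the plan's SD of 3.47, half the women lacking 5b, and a gap of 1 to 2 oocytes. The share and the gap are assumptions, and the true size is unknown. Admitting both kinds of women is a legitimate design choice. The change is worth making because it costs little and alters a method that the article already fixes.

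**What to change.** - Record 5b (yes/no) at screening for every woman, including those who already qualify on 5a + 5c.
- Replace the unadjusted primary test with one adjusted for 5b, such as ANCOVA or a van Elteren stratified rank test, and name the choice before outcome data are seen.
- If randomisation has not begun, stratify the block list by 5b, unless the full protocol already does so. If it has begun, the adjusted analysis is still available.
- Report the primary result by 5b descriptively, without subgroup claims.
- Word the target population and the conclusions as proven or predicted POR under criterion 5, and align the background wording with that.

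The cost is one yes/no field, a second block list if stratification is used, and a slightly more complex primary analysis, since a plain two-sample t test or Wilcoxon test cannot carry the adjustment. No patients or procedures are added.
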